### Monitoring

#### Data monitoring

The study was reviewed by the sponsor and felt to be of low risk on the grounds that it is not a clinical trial of an investigational medicinal product and the low likelihood of harms associated with the intervention. Therefore the creation of a data monitoring committee was not felt necessary. No interim analysis of data is planned.

#### Harms

The risks of nose and throat swabs and additional blood tests being taken are minimal and where occurring are likely to be mild. No additional adverse events s related to POCT for respiratory viruses are anticipated. However active monitoring and reporting of severe adverse events will be undertaken. Serious adverse events (SAE) are defined here as:Death during admission or within 30 days of enrolmentAdmission to the intensive care unitEvidence of prolonged hospital stayNew or persistent significant disability or incapacityEvidence of congenital anomaly or birth defect

As participants in ED are not yet hospitalised but have a reasonable likelihood of being admitted to hospital, patients enrolled in ED who are subsequently admitted to the hospital will not automatically be counted as having experienced a SAE. Participants who are already admitted to AMU are already hospitalised however, an adverse event leading to prolongation of their existing hospitalisation will be counted as an SAE.

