**Methods:**

The ResPOC study is a pragmatic randomised controlled trial of molecular point-of-care testing for respiratory viruses in adults with acute respiratory illness presenting to a large teaching hospital in the United Kingdom. Eligible participants are adults presenting with acute respiratory illness to the emergency department or the acute medicine unit. Participants are allocated 1:1 by internet-based randomisation service to either the intervention of a nose and throat swab analysed immediately on the FilmArray Respiratory Panel as a POCT or receive routine clinical care. The primary outcome is the proportion of patients treated with antibiotics. Secondary outcomes include turnaround time, virus detection, neuraminidase inhibitor use, length of hospital stay and side room use. Analysis of the primary outcome will be by intention-to-treat and all enrolled participants will be included in safety analysis.

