### Study aims and objectives

This study aims to prospectively evaluate whether use of a molecular point-of-care diagnostic test will improve clinical outcomes compared to routine clinical care, in adult patients presenting to the secondary care with acute respiratory illness. The primary objective of the study is to evaluate the impact of POCT on antibiotic use. The secondary objectives include evaluating the impact of POCT on influenza antiviral use, side room facility use, duration of hospitalisation and the turnaround time of results compared with standard laboratory based PCR.

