#### Blinding

As this is a pragmatic trial of a diagnostic device no attempt at blinding trial participants, research staff or care providers will be made. Data analysts will be blinded to group allocation.

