## Discussion

We hypothesise that molecular point-of-care testing for respiratory viruses, in adults presenting to hospital with acute respiratory infection, will reduce antibiotic use, improve detection of influenza and use of neuraminidase inhibitors, improve isolation facility use and be safe.

This study has the potential to improve patient care by changing practice and contribute to a health economic analysis. The outcome measures are clinically important to a large number of patients, and also crucial in antimicrobial stewardship and healthcare resource management. As a randomised controlled trial, this study will provide high-quality evidence for the potential use of molecular point-of-care testing for respiratory viruses in hospitalised adults. Beyond this trial, molecular point-of-care testing for common pathogens in select populations, such as in intensive care, or other common illness presentations, such as gastroenteritis, needs to be evaluated to further improve patient care and effectively manage healthcare resources.

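### The SAE definition counts an adverse event that prolongs the stay but not one that leads to re-admission, so the SAE count depends on discharge timing

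*Protocol article*

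**What the plan says.** The Harms section of the protocol article promises that "active monitoring and reporting of severe adverse events will be undertaken" and then defines an SAE by five items: death in hospital or within 30 days of enrolment, admission to intensive care, a prolonged stay, disability or incapacity, and congenital anomaly. Two explanatory sentences follow.

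- For the emergency department (ED): "patients enrolled in ED who are subsequently admitted to the hospital will not automatically be counted as having experienced a SAE".
- For the Acute Medical Unit (AMU): "an adverse event leading to prolongation of their existing hospitalisation will be counted as an SAE".

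Neither sentence mentions a patient who goes home and is admitted again. Re-presentation and re-admission within 30 days appear only under Secondary outcomes.

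Three other statements bear on the point.

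- Length of stay is something the test may change: "The secondary objectives include evaluating the impact of POCT on influenza antiviral use, side room facility use, duration of hospitalisation".
- The Discussion hypothesises that testing will "improve isolation facility use and be safe".
- The Abstract says that "all enrolled participants will be included in safety analysis".

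**The concern.** Whether a moderate complication counts as an SAE depends on where the patient is when it happens. A worsening that adds days to the current stay is on the list. The same worsening a day after discharge, treated on an ordinary ward, is not.

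That would matter little if discharge timing were unrelated to the allocated arm. Here it may be related: duration of hospitalisation is a secondary objective, and the trial is open ("no attempt at blinding trial participants, research staff or care providers will be made"), so clinicians can act on the result when deciding on discharge. An arm that goes home sooner spends fewer days in the setting where this kind of SAE can occur. Its count would be lower with no difference in harm, in a trial that includes safety in its hypothesis.

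**Working it through.** **1. Side-by-side reading.** Take one adverse event that is not fatal, needs no intensive care and leaves no disability.

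| When it occurs | Consequence | On the SAE list? | Seen elsewhere? |
|---|---|---|---|
| Before discharge | Longer index stay | Yes | Length of stay, prolonged stay |
| After discharge, within 30 days | Ward re-admission | No | 30-day re-presentation and re-admission |

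Death to 30 days, intensive care admission and disability are listed with no condition that the patient is still in the index stay, so discharge timing does not affect them.

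**2. Inputs.** The protocol gives no figure on this point: no length of stay, complication rate or onset time. The only input taken from it is the planned 360 patients per group (Sample size). Everything else below is assumed: equal true harm in both arms, onset independent of stay, and the same fraction of in-hospital complications judged to prolong the stay in each arm. The control mean stay is set at 5 days.

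**3. First model.** Stay is exponential with mean m days and onset is uniform over days 0 to 7. The share of complications starting before discharge is

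(m/7) × (1 − exp(−7/m)).

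| Mean stay m | Share before discharge | Ratio to control |
|---|---|---|
| 5 (control) | 0.714 × 0.753 = 0.538 | 1 |
| 4.5 | 0.643 × 0.789 = 0.507 | 0.94 |
| 4 | 0.571 × 0.826 = 0.472 | 0.88 |
| 3 | 0.429 × 0.903 = 0.387 | 0.72 |

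**4. Second model, as a check on the form.** Stay and time to complication are both exponential, with means m and T. The share before discharge is m/(m + T). The ratio to a 5-day control stay, for T from 3 to 10 days, is:

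- 4.5 days: 0.93 to 0.96
- 4 days: 0.86 to 0.91
- 3 days: 0.69 to 0.80
- 5 days (equal stay): 1.0 throughout

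In counts, assume a 10% complication risk, which is 36 events per arm of 360, with T = 5 and every in-hospital complication prolonging the stay. Control shows 36 × 5/10 = 18.0. The POCT arm shows 36 × 4.5/9.5 = 17.1, 36 × 4/9 = 16.0 or 36 × 3/8 = 13.5 at mean stays of 4.5, 4 and 3 days.

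**5. With re-admission counted.** If every post-discharge complication leads to re-admission, both arms show 36 and the ratio returns to 1.0.

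**6. Effect on the total.** These ratios apply to the prolongation component only. If that component is a fraction w of control SAEs, and the other items are equal between arms, the ratio for all SAEs is 1 − w(1 − r), where r is the ratio above. It is closer to 1 than r whenever w is below 1, and the documents do not give w.

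**The case against.** **The ED sentence implies that hospitalisation counts.** An exemption for admission from ED is needed only if admission would otherwise be an SAE. The Confidentiality section adds that SAEs are reported in line with Good Clinical Practice and regulatory requirements, and the article condenses a longer protocol. So the printed list may be a shortened one. This has some force, and the authors may have meant re-admission to count. But the article presents the list as the definition, and neither the ED sentence nor the general reference adds re-admission. Followed as printed, it is not an SAE. If the intention was otherwise, the remedy is the same wording.

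**The harm is measured anyway.** This stands. Thirty-day re-presentation and re-admission, mortality, intensive care or high dependency admission and prolonged stay are all secondary outcomes, and Statistical methods compares binary outcomes by chi-square. A reader might infer that the definition hides excess re-admissions under POCT. It does not, because they would appear in the trial's results.

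**No test of SAE totals is specified.** Also true. The article does not say that the safety conclusion rests on an SAE total, so one cannot conclude that the safety finding itself is biased.

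**In-trial detection.** A reader might also infer that listing re-admission would reveal an excess by arm while the trial runs. The documents do not support this. The Data monitoring section says "Therefore the creation of a data monitoring committee was not felt necessary" and plans no interim analysis, so nobody is described as comparing SAEs by arm during the trial.

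**Which harm.** It is tempting to argue that untreated bacterial infection after discharge is the most plausible harm of acting on a virus result. The documents do not say so, and the point does not need it.

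**Conclusion.** The point holds in a limited form. As printed, the SAE definition makes one class of event, the non-fatal complication without intensive care or disability, depend on discharge timing, which the trial treats as a possible effect of POCT. With equal harm and a shorter stay in the POCT arm, the prolongation component would be lower there. The direction is the same in both models. The size is illustrative: about 0.94, 0.88 and 0.72 at mean stays of 4.5, 4 and 3 days against 5 in the first model, and 0.69 to 0.96 over the ranges of the second. It is zero if stay does not differ. The distortion is confined to the SAE count and SAE reporting. It is worth correcting because safety is a stated hypothesis and the correction is cheap.

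**What to change.** 1. In Harms, add unplanned re-admission within 30 days of randomisation to the SAE list, for ED and AMU participants alike. Keep the exemption for admission from ED, and say that it covers the index admission only.
2. In the safety analysis, report by arm, over all enrolled participants, one combined item: prolongation of stay due to an adverse event, or unplanned re-admission. Discharge timing then moves an event between the two halves of the item and not out of the count.

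This changes safety definitions and reporting only. Thirty-day re-admission is already collected. The listed outcome does not say whether its 30 days run from randomisation or from discharge, but either window covers the period needed. The cost is protocol wording and more SAE forms. If the extra forms are judged too heavy, reporting the combined item beside the SAE table would still remove the distortion from the final comparison.

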#### Auditing

Regular monitoring will be performed according to ICH GCP by the sponsor. Data will be evaluated for compliance with the protocol and accuracy in relation to source documents. Following written standard operating procedures, the monitors will verify that the clinical trial is conducted and data are generated, documented and reported in compliance with the protocol, GCP and the applicable regulatory requirements.

### Protocol amendments

All protocol modifications were communicated to investigators and to trial registries. Two amendments to the protocol have been approved by the ethics committee, the first, to change the study from a pilot study into a full study and to amend an exclusion criterion, the second, to add a laboratory analysis plan for the samples collected (current protocol version 3.0, date 26th January 2016). The local study reference is RHM MED1217.

### Confidentiality

All data will be anonymised to protect participant confidentiality: volunteer participant data will be identified by a unique study number in the case report forms and database. Serious Adverse Events will be reported in line with Good Clinical Practice and regulatory requirements. All study staff are trained in Good Clinical Practice. Only the investigators and sponsor’s representative (monitor) have access to the data, which is kept securely.

### Access to data

The final data set will be wholly accessible to the principal investigator, co-investigators and independent statistician and may be made available to other parties on request.

### Dissemination policy

Authorship of this and subsequent manuscripts stemming from this protocol will follow the ICMJE recommendations, and CONSORT statement where appropriate, and there is no intent to use professional writers. There are no plans to make the dataset publically available. Beyond the study team and regulatory oversight, the full protocol is only made available at the discretion of the chief investigator. The data and samples collected are expected to form multiple publications, and these publications must acknowledge this trial and study team as appropriate.

## Discussion

We hypothesise that molecular point-of-care testing for respiratory viruses, in adults presenting to hospital with acute respiratory infection, will reduce antibiotic use, improve detection of influenza and use of neuraminidase inhibitors, improve isolation facility use and be safe.

This study has the potential to improve patient care by changing practice and contribute to a health economic analysis. The outcome measures are clinically important to a large number of patients, and also crucial in antimicrobial stewardship and healthcare resource management. As a randomised controlled trial, this study will provide high-quality evidence for the potential use of molecular point-of-care testing for respiratory viruses in hospitalised adults. Beyond this trial, molecular point-of-care testing for common pathogens in select populations, such as in intensive care, or other common illness presentations, such as gastroenteritis, needs to be evaluated to further improve patient care and effectively manage healthcare resources.

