### Trial design

This is a pragmatic randomised controlled trial with parallel groups allocated 1:1 to the intervention (POCT) and control (routine clinical care) arms. The framework is superiority. The study protocol adheres to the SPIRIT statement [50].

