#### Sample size

Sample size is based upon the primary outcome measure of proportion of patients treated with antibiotics. Previous studies have demonstrated that around 75% of patients hospitalised in the UK with acute respiratory illness are treated with antibiotics [2]. Two small studies in hospitalised adult patients with acute respiratory illness have demonstrated reductions in the proportion of patients treated with antibiotics of around 10–15% in those tested for respiratory viruses [44, 52]. To detect a reduction in antibiotic use from 75 to 65% with a power of 0.8 and significance level of 0.05, 326 patients would be required in each group. Allowing for withdrawals in up to 10% of patients we aim to recruit 360 patients to each group (720 patients in total).

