#### Statistical methods

This will be performed by a dedicated medical statistician from the University of Southampton independent from the study team. Patients tested with the rapid diagnostic test will be compared with patients treated by routine clinical care using standard descriptive and comparative statistical methods using Prism (GraphPad Software Inc; La Jolla, California) and SPSS (SPSS, Inc; Chicago, Illinois). Summaries of all baseline characteristics will be presented using means and standard deviations, medians and interquartile ranges, or frequencies and percentages, as appropriate. Analysis of the primary outcome will be by intention-to-treat and will compare the proportion of patients receiving antibiotics using the chi-square test for equality of proportions between groups. The effect of group (intervention or control) on the primary outcome will be further assessed using logistic regression to control for demographics (age, sex) and other co-variables. For secondary outcomes the intervention and control groups will be compared using chi-square tests for equality of proportions for binary data (including proportions) and using t-tests and non-parametric equivalent tests for continuous data (e.g. turnaround time) as appropriate.

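### The protocol hypothesises that point-of-care testing will be safe, but the only comparison it states for the binary harm outcomes is a test of equality, which cannot support that hypothesis

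*Protocol article*

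**What the plan says.** All references are to the protocol article.

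- **Discussion.** Safety is part of the study hypothesis, beside lower antibiotic use and better influenza detection and treatment: POCT will "improve isolation facility use and be safe". No test or criterion is attached.
- **Trial design.** "The framework is superiority".
- **Secondary outcomes.** The list includes mortality (in hospital and at 30 days), ICU or HDU admission, and re-presentation and re-admission within 30 days. All are proportions.
- **Statistical methods.** Secondary outcomes are compared "using chi-square tests for equality of proportions for binary data (including proportions"). No other comparison is stated for binary secondary outcomes.
- **Sample size.** The calculation concerns the primary outcome only: "To detect a reduction in antibiotic use from 75 to 65" per cent.
- **Abstract, Methods.** "all enrolled participants will be included in safety analysis". This fixes a population, not a method.
- **Harms.** Serious adverse events are actively monitored and reported. Death and ICU admission are both serious adverse events and secondary outcomes.

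**The concern.** A chi-square test of equality asks whether the data contradict equal risks. It can show that POCT changes mortality or re-admission. It cannot show that POCT leaves them acceptably unchanged, because a large p-value may reflect either similar risks or too few events. A claim of safety needs an increase of some stated size to be excluded, which is a question for an interval estimate.

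This matters because the background section expects POCT to work by preventing antibiotic use once a virus is identified. The harm of interest therefore includes possible under-treatment as well as the minor risks of swabbing. There is no data monitoring committee and no interim analysis, so the final comparison carries most of the weight. The authors also say that the trial could change practice. If the report offers only p-values for these outcomes, a reader cannot tell how large an increase remains compatible with the data.

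**Working it through.** **1. The plan's own figure.** The inputs from Sample size are 75% v 65%, power 0.8 and significance level 0.05 (taken as two-sided). Trial design gives 1:1 allocation. The unpooled two-proportion formula is

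n = (1.960 + 0.842)² × [0.75×0.25 + 0.65×0.35] / 0.10² = 7.849 × 0.415 / 0.01 = 325.7, so 326 per group.

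This matches the stated 326. The recruitment target of 360 per group allows for withdrawals. The calculation is sound for antibiotic use and involves no harm outcome.

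**2. What the equality test can detect.** The article gives no expected rate for any harm outcome in this population. Control risks of 3%, 5% and 15% are therefore assumptions that span rarer and commoner events. With n = 360 per arm, two-sided 0.05 and p̄ the mean of the two risks p₁ and p₂:

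power = Φ{ [|p₂ − p₁| − 1.96√(2p̄(1−p̄)/n)] / √[(p₁(1−p₁) + p₂(1−p₂))/n] }

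For 3% v 6%: [0.0300 − 0.0303] / 0.0154 = −0.018, so power = Φ(−0.018) = 0.49.

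**3. What an interval would show.** If both arms have risk p, the 95% half-width of the risk difference is 1.96√(2p(1−p)/n). For p = 3%: 1.96√(2×0.03×0.97/360) = 0.0249, or 2.5 points.

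| Assumed control risk | Power, 1.5-fold rise | Power, doubling | Intervention risk detectable with 80% power | 95% half-width, equal risks |
|---|---|---|---|---|
| 3% | 18% | 49% | 7.7% | 2.5 points |
| 5% | 28% | 72% | 10.6% | 3.2 points |
| 15% | 73% | 99.8% | 23.2% | 5.2 points |

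With 326 per arm instead of 360, power for a doubling falls to 46% at 3% and 68% at 5%. It stays above 99% at 15%.

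**4. Illustration (invented counts).** Take 11/360 events in the control arm and 21/360 in the POCT arm, that is 3.1% v 5.8%. The chi-square test without continuity correction gives p = 0.07. The risk difference is 10/360 = 2.8 points. Its standard error is √[(0.0306×0.9694 + 0.0583×0.9417)/360] = 0.0153, so the 95% interval is 2.8 ± 3.0, from −0.2 to +5.8 points. The test alone says not significant. The interval shows that an increase of nearly 6 points has not been excluded.

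**5. Would a composite help?** Pooling events into one composite does not narrow the absolute interval, because below 50% the half-width grows with the event rate. If the components ran at 3%, 5% and 15%, the composite would lie between 15% (complete overlap) and 3 + 5 + 15 = 23% (no overlap). Its half-width would be 5.2 to 1.96√(2×0.23×0.77/360) = 6.1 points, no narrower than for any single component.

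**The case against.** The strongest objection is that the article contains no decision rule for safety. A reader might infer that the investigators will declare POCT safe if the chi-square tests are non-significant. The text does not support that. The Discussion names no test, the Statistical methods section does not mention safety, and the Abstract refers to a safety analysis without a method. The link between the hypothesis and these tests is an inference from which outcomes the rule covers. This part of the objection stands.

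It is also fair that the article condenses a fuller protocol. A margin or an interval criterion may be given there or in an analysis plan, and listing chi-square tests does not forbid confidence intervals. The absence of a margin is therefore no fault. What remains is a pairing that the article itself makes: a safety hypothesis, and one stated method for the relevant binary outcomes that cannot address it.

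Three further points stand:

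- Safety is not among the listed objectives. Re-presentation, re-admission and HDU admission are not in the serious adverse event definition, so treating them as harm outcomes is a reasonable reading, not the article's label.
- Sizing a trial on its primary outcome is normal practice and not a defect.
- The event risks are assumed. At 15% the test would almost always detect a doubling, so low power is a problem of the rarer outcomes. Even there, a non-significant result would not by itself say what increase is excluded.

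**Conclusion.** The point holds as a mismatch between a stated hypothesis and the stated analysis. It is not a finding that safety will be judged by p-values. No comparison in the article could support the claim that POCT is safe, and for rarer outcomes the equality test could easily miss a material increase. At an assumed 3% control risk it would miss a doubling about half the time, and at 5% about 28% of the time (360 per arm, two-sided 0.05). Intervals of about ±2.5 to ±5.2 points are what the trial can offer if true risks are equal and lie between 3% and 15%. All of these figures depend on the assumed risks.

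The weight is moderate. The primary analysis is unaffected, serious adverse events are monitored, and no redesign or larger sample is called for. The change is still worth making before the results are written up.

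**What to change.** For mortality, ICU/HDU admission, re-presentation and re-admission, report the risk difference (POCT minus routine care) with its 95% confidence interval, by randomised group, and make that the basis of any safety statement. Word the conclusion as the size of increase that the upper limit excludes, outcome by outcome. The chi-square p-values may stay beside the intervals but should not carry the conclusion.

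The alternative is to make the hypothesis descriptive, for example by stating that the trial will describe and compare harm outcomes between arms.

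Do not add a composite in the hope of a tighter risk difference, since its higher event rate would widen the absolute interval.

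The data are already to be collected, so the cost is a few lines of analysis and wording. The one downside is a weaker statement: the report could say which increases are unlikely, not that POCT is safe.
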